In particular, the first aim will be to assess the short-term and long-term efficacy of tele@cognitive protocol as compared to an unstructured cognitive at-home rehabilitation in the treatment of a cohort of patients with CNDs, monitoring intervention effectiveness by a clinical, functional, neurocognitive, and quality of life assessment applied before treatment (T0), after treatment (5 weeks, T1), and at a 3-month follow up visit (T2). We hypothesize that this digital health at-home intervention would ameliorate cognitive abilities more than unstructured at-home rehabilitation in subjects with SCCs, MCI, and PD. We will also evaluate adherence to the rehabilitation program delivered at-home in the absence of therapist supervision. It is hypothesized that, at an early stage of the disease, cognitive telerehabilitation treatment with innovative digital solutions can bring about positive effects on treatment adherence and difficulties specific to each clinical condition.

The second aim will be to investigate the effects of a cognitive rehabilitative protocol based on a digital health at-home intervention (tele@cognitive) on biomolecular and neurophysiological markers, hypothesizing that people with CNDs enrolled in the tele@cognitive protocol will develop changes in circulating biomarkers and patterns of connectivity. Specifically, at T0 and T1, we will study the effect of tele@cognitive treatment on: i) blood biomarkers reflecting neurodegeneration, amyloid-β, tau and alpha-synuclein pathologies, neuroinflammation, synaptic function, and neuronal communication; ii) neurophysiological responses to TMS over the motor cortex. This approach will give a broad overview of the circuits modulated through telerehabilitation (tele@cognitive treatment), possibly highlighting differential effects between the groups.

Finally, the third aim will be to investigate potential cognitive, neurobiological, and neurophysiological predictors of treatment outcomes in people with CNDs who received innovative technology-enhanced telerehabilitation intervention (tele@cognitive group).

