The unstructured cognitive rehabilitation treatment applied in the ACG will offer paper–pencil cognitive activities that will stimulate the same cognitive abilities indicated in the innovative digital solution. Subjects assigned to ACG will be requested to work for the same duration and frequency as the tele@cognitive group; they will receive from the therapist an instructions booklet and a participant diary.

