### 2.7. Data Collection

Demographic characteristics and cognitive reserve, evaluated with the Cognitive Reserve Index—questionnaire (CRI-q [116]), will be collected at the baseline evaluation (T0). The same trained neuropsychologist (blinded to patient treatment allocations) will assess primary and secondary outcome measures for a single patient in all visits (T0, T1, and T2). Neurophysiological and biomolecular data will be collected only at the baseline (T0) and at post-treatment (at 5 weeks, T1). A subjective assessment of the digital system’s usability will be performed at T1 using the System Usability Scale (SUS) [117], a 10-item attitude Likert scale. Best practices and standards will be adopted for the collection, storage, and treatment of the data. Clinical, functional, neurocognitive, and quality of life assessment data will be collected by clinicians and stored in a specific dataset. Data will be pseudo-anonymized so that they will not be linkable to the identities of the subjects. Neurophysiological data will be organized according to Brain Imaging Data Structure (BIDS) for non-invasive brain stimulation studies and safely stored in a dataset. Biological samples collected at T0 and T1 will be stored at −80 °C until the analyses. Biomolecular data will be safely stored in a dataset. Informed consent will be obtained from patients for the storage of all data. In more detail, the data collection in terms of data collected and tools will include:

[AIM1] Clinical, functional, neurocognitive, and quality of life data recorded at T0 (baseline), T1 (post-treatment, at 5 weeks), and T2 (3-month follow-up visit).

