### 2.8. Statistical Analysis

A repeated-measures analysis will be used to compare pre-treatment (T0) versus post-treatment (T1) and follow-up (T2) clinical, functional, neurocognitive, and quality of life variables for the two groups. Neurophysiological and biochemical data will be analyzed using repeated-measures ANOVAs by comparing the data recorded at T0 and T1. Statistical tests suitable for the data type will be employed to assess the differences between the groups. For continuous variables, independent *t*-tests will be utilized, while chi-square tests will be applied for categorical variables [117,118]. This analysis will verify the effectiveness of the randomization procedure, ensuring that any subsequent comparisons or evaluations between the groups are reliable and valid.

Within-group analyses will be conducted for the tele@cognitive and ACG groups to examine changes from T0 to T1 and T2. Paired *t*-tests or Wilcoxon signed-rank tests, depending on data distribution, will be employed to assess the effectiveness of the intervention over time by analyzing the variations in the collected multimodal parameters [118,119]. Furthermore, a between-group analysis will be conducted to quantitatively compare the outcomes of the two groups. Statistical tests such as independent *t*-tests, analysis of covariance (ANCOVA), or non-parametric tests will be employed, depending on the distributional assumptions and nature of the outcome variables [118,120].

In addition to these statistical analysis, predictive modeling will be implemented to identify key factors associated with treatment outcomes by integrating multimodal data from cognitive assessment, neurophysiological evaluations, biomolecular patterns, and user interaction data within a sophisticated AI framework. Given the heterogeneous nature of the data collected from multiple sources, feature selection is essential to identify the most informative features and reduce dimensionality. This step is critical to eliminate redundant or irrelevant variables and improve model performance [121]. Statistical methods such as chi-square tests and mutual information will be employed to identify significant predictors associated with positive treatment outcomes [122]. Specifically, the dataset will include baseline clinical, functional, neurocognitive, and quality of life measures, biomolecular markers, and neurophysiological parameters.

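### Section 2.8 gives within-arm before/after tests the job of assessing effectiveness, which only the randomised between-group contrast can do

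*Protocol article*

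**What the plan says.** The second paragraph of section 2.8 states: "Within-group analyses will be conducted for the tele@cognitive and ACG groups to examine changes from T0 to T1 and T2". It names paired t-tests or Wilcoxon signed-rank tests for this, chosen by data distribution, and says that they "will be employed to assess the effectiveness of the intervention over time". The next sentence but one adds the comparison: "Furthermore, a between-group analysis will be conducted to quantitatively compare the outcomes of the two groups", by independent t-test, ANCOVA or a non-parametric test. The section opens with a repeated-measures analysis of T0, T1 and T2 for the two groups.

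Other parts of the article bear on how the paired tests can be read:

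- **Hypothesis (section 1).** It is comparative: "this digital health at-home intervention would ameliorate cognitive abilities more than unstructured at-home rehabilitation".
- **Sample size (section 2.3).** It rests on a two-tailed independent-samples t-test on MoCA increase, with a between-arm effect of d = 0.784.
- **Control (section 2.5).** The control is active. Its paper-and-pencil tasks "will stimulate the same cognitive abilities indicated in the innovative digital solution", for the same duration and frequency.
- **Repeated testing (section 2.7).** The same blinded neuropsychologist assesses each patient's primary and secondary outcomes at T0, T1 (5 weeks) and T2 (3-month follow-up).

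**The concern.** In section 2.8 the intervention's effectiveness is tied by name to the within-arm tests only. The one other use of the word there concerns the randomisation procedure. A paired test asks whether an arm's mean change differs from zero. In this design that change can have several sources besides the digital treatment: familiarity with tests taken up to three times, regression to the mean, time, and the non-specific effects of doing any cognitive exercise at home. All of these can act in both arms. Randomisation removes them from the difference between arms, but not from the change within one.

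What is at stake is the reporting of aim 1. If the between-group result is null and the tele@cognitive paired test is significant, the text as written gives an author grounds to call the intervention effective. The Discussion expects the results to lead to a recommendation for use, so that reading would matter even in a pilot.

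**Working it through.** **1. The plan's own figure, and which contrast it is for**

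Inputs from section 2.3: d = 0.784, two-sided alpha 0.05, power 0.80 (reading the printed beta of 0.80 as power), 30 per group including drop-out. The drop-out rate is not given.

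- Normal approximation: n per arm = 2(1.960 + 0.842)² / 0.784² = 25.5, so 26.
- Exact noncentral t: 26 per arm gives power 0.792 and 27 gives 0.807, so 27 per arm, 54 in total.
- With an assumed drop-out of 10%: 54 / 0.90 = 60, the stated total. An assumed 0%, 5% or 15% gives 54, 57 or 64.

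The 60 therefore reproduces, at an assumed 10% drop-out, as the size for a between-group test. The within-arm tests play no part in it.

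**2. What the paired test does when the arms are identical**

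Assume that both arms have the same mean change, δ, in SD units of the change score, so that the true between-arm effect is zero. The article gives no retest gain or spontaneous change, so δ is an assumption, shown from 0.1 to 0.5. Use n = 27 (the analysable number from step 1) and n = 30 (full retention).

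P(significant improvement in one arm) = P(T > t₀.₉₇₅ with n − 1 df), where T is noncentral t with n − 1 df and noncentrality δ√n. For example, δ = 0.3 and n = 27 gives 0.3 × √27 = 1.56 and a probability of 0.323.

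| Shared change δ (SD of change score) | n = 27 | n = 30 |
|---|---|---|
| 0 | 0.025 | 0.025 |
| 0.1 | 0.072 | 0.076 |
| 0.2 | 0.169 | 0.184 |
| 0.3 | 0.323 | 0.355 |
| 0.4 | 0.517 | 0.563 |
| 0.5 | 0.706 | 0.754 |

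The between-arm test does not depend on δ. Its two-sided error is 5%, or 2.5% in favour of tele@cognitive.

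**3. Can the two results disagree in one trial?**

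In 100,000 simulated trials with n = 30 per arm and identical arms, the between-group test was significant in about 5% (0.051 at δ = 0.2, 0.049 at δ = 0.5). Among trials with a non-significant between-group test, the tele@cognitive paired test still showed significant improvement in 17% at δ = 0.2 and 77% at δ = 0.5. A null between-arm result therefore gives little protection against a positive paired test.

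**The case against.** The strongest reply is that the comparative analysis is planned and underlies the design. Section 2.8 opens with a repeated-measures analysis for the two groups, the same paragraph as the paired tests adds a between-group analysis, and the hypothesis and sample size are both comparative. This stands: no comparison is missing. Nor does the connective that introduces the between-group analysis rank it below the paired tests, since order of mention is not a hierarchy.

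A reader might go further and infer that the plan will declare efficacy from a significant paired test, or from significance in tele@cognitive but not in the control. The article states no such rule and plans no comparison of the two within-arm p-values. Under identical arms with n = 27 and δ = 0.3 to 0.5, significance in tele@cognitive only has probability p(1 − p), or 21–25%, and significance in at least one arm has 1 − (1 − p)², or 54–91%. These figures show what such a misreading would cost. They are not the plan's own error rate.

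It can also be said that the sentence merely describes each arm's course over time. That reading is possible, but the sentence names significance tests and gives their object as the intervention's effectiveness, so it needs correcting on either reading. A full analysis plan may name the decisive contrast. That would not cure the published sentence, which states a wrong use and does not merely leave out detail.

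Finally, the size depends on δ, for which the documents give nothing. At 0.1 SD the excess is modest (7–8% against 2.5%). That is why the whole range is shown.

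**Conclusion.** The concern holds in limited form: wrong as written, and it should be fixed. Section 2.8 gives within-arm tests a purpose that they cannot serve against a comparative hypothesis, an active control and repeated testing. With identical arms, 27–30 analysed per arm and a shared gain of 0.1 to 0.5 SD of the change score, the tele@cognitive paired test shows improvement in about 7–8% to 71–75% of trials, against 2.5% for the between-arm test in that direction. The shared gain and the 27 analysable patients per arm are assumptions. That a paired test cannot isolate the treatment effect depends on neither.

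The point does not rank higher because the right comparison is already planned, the sample size is built on it, and no faulty decision rule is stated.

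**What to change.** Reword section 2.8, and carry the same wording into the analysis plan, to say two things:

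- Effectiveness is judged only on the randomised between-group contrast, as a baseline-adjusted difference or a group-by-time effect, with its 95% confidence interval.
- Within-arm changes from T0 to T1 and T2 are reported descriptively with confidence intervals and are not evidence of effectiveness.

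Within-arm p-values need not be banned. It is enough that no effectiveness claim rests on them. The cost is a few sentences: the sample size, visits and data collection stay as they are.

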### 2.2. Randomization and Blinding

The assigned group will be obtained by stratified randomization (1:1 ratio), according to clinical condition, age, and his/her performance in the Montreal Cognitive Assessment (MoCA) test [94,95,96]. Stratified randomization will be achieved by generating a separate block for each combination of covariates, and participants will be assigned to the appropriate block of covariates by a researcher blinded to the study’s aims. Details of the allocated group will be given on cards contained in sequentially numbered, opaque, and sealed envelopes. A blinded researcher will conduct the evaluations.

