### 2.3. Sample Size

In the RCT, patients will be assigned to either receive tele@cognitive protocol or a home-based unstructured cognitive stimulation (ACG). The sample size of the present study was estimated on the basis of a previous work on people within the Alzheimer’s Disease continuum [3] and it was computed on a primary outcome variable (an increase in MoCA score). Applying a two-tailed independent samples *t*-test (alpha = 0.05, beta = 0.80) and considering the effect size (d = 0.784) between two types of intervention (tele@cognitive vs. ACG), we obtained a minimum sample size of 60 subjects (30 per group), taking into account the drop-out rate.

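### No single between-group analysis is fixed for MoCA, so baseline adjustment is optional, the strata go unused, and baseline p-values are wrongly taken to verify randomisation

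*Protocol article*

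**What the plan says.** All places are in the protocol article.

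- **Clinical and cognitive outcomes (section 2.8).** A repeated-measures analysis over T0, T1 and T2 comes first. A separate between-group comparison follows, with independent t-tests, "analysis of covariance (ANCOVA), or non-parametric tests will be employed, depending on the distributional assumptions and nature of the outcome variables". The list is introduced as examples, and nothing ranks its members or places them above or below the repeated-measures analysis.
- **Blood and TMS outcomes (section 2.8).** "Neurophysiological and biochemical data will be analyzed using repeated-measures ANOVAs by comparing the data recorded at T0 and T1".
- **Baseline comparisons (section 2.8).** Between-group t-tests and chi-square tests are planned, and the text says: "This analysis will verify the effectiveness of the randomization procedure". It adds that this secures the reliability and validity of later group comparisons.
- **Allocation (section 2.2).** Patients are assigned by "stratified randomization (1:1 ratio), according to clinical condition, age, and his/her performance in the Montreal Cognitive Assessment (MoCA) test". Section 2.8 does not return to these factors.
- **Planning test (section 2.3).** The size rests on an increase in MoCA: "Applying a two-tailed independent samples" t-test, "alpha = 0.05, beta = 0.80", "considering the effect size (d = 0.784) between two types of intervention".

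**The concern.** Three things need attention.

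1. **No deciding analysis.** A group-by-time effect, a difference in mean change, a baseline-adjusted difference and a rank shift are different quantities, and they can give different p-values in the same 60 patients. If the article does not say which one decides MoCA, a reader of the results cannot tell whether the reported test was the intended one.
2. **Baseline and strata are not built in.** Baseline MoCA, condition and age are used to allocate patients and are already recorded. Adjusting for them is the natural counterpart in the analysis, but it happens only if the ANCOVA option is taken, and that option's covariates are not named. For blood and TMS outcomes the method is fixed, and it is the less efficient one.
3. **The randomisation check is a wrong statement, not an omission.** If allocation was sound, every significant baseline difference is chance. If the test is not significant, that does not show balance. Neither result bears on the validity of the later comparisons.

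**Working it through.** **Inputs from section 2.3.** Two-sided alpha 0.05, d = 0.784, 30 per arm. The printed beta of 0.80 is read as power 0.80, because power of 0.20 would need only 5 per arm. Not given: the dropout rate, the SD on which d is standardised, and the T0–T1 correlation rho. The last is assumed to be 0.5–0.8.

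**1. The plan's own figure.** A two-sample t-test with d = 0.784, alpha 0.05 and power 0.80 needs 26.53 per arm by the noncentral t distribution, so 27 per arm and 54 evaluable. With an assumed 10% dropout, 27/0.90 = 30 per arm, or 60 in total, which is the stated size. Other rates give 29 (5%), 32 (15%) or 34 (20%) per arm. Power of the unadjusted t-test is 0.807 at 27 per arm and 0.848 at 30.

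**2. Two-visit repeated-measures ANOVA.** With two groups and two visits, the group-by-time F statistic is the square of the t statistic comparing mean change between groups. With equal variance s² at both visits:

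- variance of a change score: 2s²(1 − rho)
- residual variance in ANCOVA: s²(1 − rho²)
- ratio, ANCOVA to change: (1 − rho²) / [2(1 − rho)] = (1 + rho)/2

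**3. What this means for the MoCA test sized in section 2.3**, if d is on the change-score SD. The effective size is 0.784/√[(1 + rho)/2].

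| rho (assumed) | Variance ratio | Effective d | Power at 27 per arm | Evaluable per arm for 80% |
|---|---|---|---|---|
| t-test on change | 1 | 0.784 | 0.807 | 27 |
| 0.5 | 0.75 | 0.905 | 0.904 | 21 |
| 0.6 | 0.80 | 0.877 | 0.885 | 22 |
| 0.7 | 0.85 | 0.850 | 0.866 | 23 |
| 0.8 | 0.90 | 0.826 | 0.846 | 24 |

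The table counts baseline MoCA only and ignores the small loss of degrees of freedom. If d were on the post-score SD, the ratio against a post-score t-test would be 1 − rho², and power at 27 per arm would be 0.904 at rho 0.5 and higher above that. The power column applies to MoCA. For blood and TMS outcomes only the variance ratio carries over, because no effect size is given for them.

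**4. The open list.** A null simulation (27 per arm, bivariate normal, 15,000 runs) took the smallest p-value among a change t-test, ANCOVA and a Mann–Whitney test on change. Type I error was 7.8% at rho 0.5 and 7.2% at rho 0.7. Adding a post-score t-test gave 10.0% and 10.6%. This is the ceiling for deliberate selection, not an estimate of what the stated rule would do.

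**5. Baseline tests.** With k independent tests under sound randomisation, the chance of at least one p < 0.05 is 1 − 0.95^k: 23% for k = 5, 40% for k = 10, 64% for k = 20. Correlated scores change these figures, and section 2.8 does not say how many variables are tested. In the other direction, a t-test with 30 per arm becomes significant only when the observed difference exceeds 2.00 × √(2/30) = 0.52 SD. A baseline gap of half an SD would therefore pass as balance.

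**The case against.** Much can be said for the plan, and several stronger readings fail.

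- **Baseline is ignored or discarded.** A reader might infer this, but it is not so. The primary outcomes in section 2.6.1 are changes from T0, the repeated-measures analysis includes T0, and ANCOVA is on the list. Baseline adjustment is optional and its covariates are unnamed; no more than that can be said.
- **The trial is underpowered without adjustment.** It is not. The unadjusted t-test reaches the plan's 80% at 27 per arm.
- **The test will be picked once the results are visible.** The article does not say so. The sentence covers bounded scores, times, error counts and categorical items, and outcome type is known beforehand. A rule applied blind to group would inflate the error far less than the simulated ceiling. What stands is that no test, diagnostic or hierarchy is given for MoCA.
- **Omitting the strata distorts the error rate by a known amount.** An unadjusted test after effective stratification errs on the conservative side. From 2[1 − Φ(1.96/√(1 − R²))], the actual level would be 0.039, 0.028 or 0.019 if the strata explained 10%, 20% or 30% of outcome variance. The article gives no such share, and the formula needs full balance within cells, which 60 patients spread over three factors may not provide.
- **Covariate lists belong in an analysis plan that is not shown.** This is fair, and it makes the strata the weaker part of the point. It does not cover the ANOVA stated for blood and TMS data or the claim about verifying randomisation, because both are positive statements.
- **The trial is a pilot.** True, but it has an efficacy aim and a powered primary outcome, and the fix is wording.

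**Conclusion.** The point holds in a limited form. Section 2.8 fixes no deciding analysis for MoCA, leaves baseline adjustment optional and does not use the stratification factors. It commits blood and TMS outcomes to a method equivalent to a t-test on change. Its statement that baseline tests verify randomisation is wrong however the rest is specified.

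For an assumed rho of 0.8–0.5, ANCOVA has 10–25% less variance than a change-score analysis. For MoCA this lifts power from 0.81 to about 0.85–0.90 at 27 per arm, assuming about 10% dropout and d on the change-score SD. That is a gain over a plan that already meets its target. The open choice of test has no determinable error rate from the article; 7–11% is a worst case only.

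**What to change.** 1. Name one primary analysis for MoCA at T1: ANCOVA, or a mixed model with arm, visit and arm-by-visit from which the T1 contrast is taken. Adjust for baseline MoCA, clinical condition and age, and report the adjusted difference with its 95% CI. Baseline MoCA as a continuous covariate also covers the MoCA stratum. Adjustment for site is optional, since allocation is not stratified by it.
2. Label the t-tests and rank tests as sensitivity analyses.
3. For blood and TMS outcomes, replace the two-visit repeated-measures ANOVA with ANCOVA of the T1 value on arm and the T0 value.
4. Delete the baseline significance tests and the sentence about verifying randomisation; present baseline data by arm descriptively.

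**Cost.** Wording, settled before outcome data are seen, and a few degrees of freedom. Baseline MoCA (1), condition (2) and age (1, if linear) take the residual from 52 to 48 with 54 evaluable patients. Sample size, visits and measurements do not change.

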### 2.5. Intervention Procedures

The cognitive rehabilitation protocol (5 weeks, 3 sessions/week, 45 min/session) will be delivered to all participants according to the corresponding experimental group:-30 CNDs patients will receive home-based cognitive rehabilitation activities with an innovative digital solution for remote rehabilitation of cognitive difficulties (tele@cognitive group);-30 CNDs patients will receive home-based unstructured cognitive rehabilitation treatment (Active Control Group—ACG).

The technological solution that will be applied in the tele@cognitive group consists of: (a) a telemedicine platform (RICORDO platform), which allows prescription and planning of digital content for cognitive rehabilitation and monitoring of the rehabilitation cycle and (b) RICORDO application [http://www.ricordo-dtx.com/ (accessed on 10 January 2025)] that will be downloaded on tablets provided to patients by the recruiting units, which will allow the patient to benefit from personalized rehabilitation treatment remotely and in asynchronous mode. In detail, through RICORDO platform, the clinician will have the possibility of prescribing, within the patient’s Individual Rehabilitation Plan (PRI), a personalized intervention that will involve the use of libraries of digital rehabilitation content that maps all the neurocognitive domains provided for in the most recent version of the Diagnostic and Statistical Manual of Mental Disorders (DSM-5) [102]. In particular, the rehabilitation program will include cognitive activities focused on cognitive domains, such as executive functions, memory (long-term memory of both verbal and visuospatial type, autobiographical memory, and semantic memory), attention (selective attention and divided attention), and spatial–temporal orientation and language. Each cognitive exercise will be structured into five levels of difficulty that adaptively increase (algorithms on both subject’s performance and perceived difficulty). All data on patient progress and adherence will be collected and will be available to evaluate and monitor the results of rehabilitation.

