[AIM3] By employing a diverse range of data collection instruments and analysis techniques, we aimed to gain a comprehensive understanding of treatment effects on cognitive function. In particular, this multifaceted approach involves capturing and analyzing various aspects related to cognitive performance: clinical, functional, neurocognitive, and quality of life measures, biochemical data derived from blood samples, different parameters derived from TMS experiments, and the data gathered during the rehabilitation program.

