In this context, our telerehabilitation protocol represents an ideal solution to provide intensive, long-lasting cognitive rehabilitation and to sustain treatment adherence, as well as to modify daily care routines. We expect that the findings of the present RCT will result in a recommendation of the use of a usable, safe, and effective way for changing CNDs’ behavior patterns, triggering mechanisms at the neurophysiological and neurobiological levels. The added value of this trial consists of: (i) adopting an asynchronous model of care out of the clinic, bypassing typical barriers obstructing accessibility to care structures and lowering system overburdening and costs; (ii) investigating the potential neurobiological and neurophysiological markers of the effects of the at-home tele@cognitive treatment; (iii) investigating potential cognitive, neurobiological, and neurophysiological predictors of response to the treatment, helping in the development of useful treatment pathways for patients with CNDs. It is necessary to clarify which types of patients can benefit the most from rehabilitation interventions and, above all, to pursue a more precise characterization of the specific intervention procedures. However, we acknowledge that the present RCT study has some limitations. In particular: a larger sample size might allow us to account for individual differences that could influence the efficacy of the treatment; we have not planned a cost-effective analysis of the telerehabilitation approach [168]; longer follow-up visits should be useful in following the progress of the improvement obtained after treatment. Moreover, it would have been useful to administer a scale that measured subjective experience and the attractiveness (hedonic quality) of the technology (e.g., UEQ scale; [169,170]).

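### The article contradicts itself on whether the Aim 3 predictors of response include app data gathered during treatment; the main model should use T0 variables only

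*Protocol article*

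**What the plan says.** Four places in the protocol article bear on what enters the Aim 3 model.

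- The Introduction sets the third aim: to "investigate potential cognitive, neurobiological, and neurophysiological predictors of treatment outcomes in people with CNDs who received innovative technology-enhanced telerehabilitation intervention". User interaction is not among the predictor classes named.
- Section 2.7, under Aim 3, lists the sources to be captured and analysed. They end with "different parameters derived from TMS experiments, and the data gathered during the rehabilitation program".
- Section 2.8 opens its modelling paragraph by "integrating multimodal data from cognitive assessment, neurophysiological evaluations, biomolecular patterns, and user interaction data within a sophisticated AI framework".
- The last sentence of that paragraph, four sentences later, states that "the dataset will include baseline clinical, functional, neurocognitive, and quality of life measures, biomolecular markers, and neurophysiological parameters". User interaction data are not in this list.

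On the nature of the app data, section 2.5 says: "Each cognitive exercise will be structured into five levels of difficulty that adaptively increase". The adaptation follows the patient's performance and perceived difficulty, and the platform stores progress and adherence. On purpose, the Discussion says: "It is necessary to clarify which types of patients can benefit the most from rehabilitation interventions".

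**The concern.** A predictor of response is useful for identifying suitable patients only if it is known before treatment starts. App data are not: they come into being during the five weeks of treatment. If they enter the model, its accuracy describes how well outcome can be read once treatment is under way, which is a different question from who benefits.

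The ranking of predictors is also at stake. Section 2.8 plans SHAP values to show which factors are most influential. Suppose a baseline marker works by letting patients perform better in the exercises. Once exercise performance is in the model, that marker can look unimportant. A reader would then dismiss a blood, TMS or cognitive marker that does carry information before treatment.

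**Working it through.** The article attaches no figure to this point, so the check is a comparison of the sections, followed by an illustration with assumed correlations.

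**1. Predictor set, side by side**

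| Place | Inputs named | App data included? |
|---|---|---|
| Introduction, third aim | cognitive, neurobiological, neurophysiological | not named |
| 2.7, Aim 3 | clinical and cognitive measures, blood, TMS, programme data | yes |
| 2.8, start of modelling paragraph | cognitive, neurophysiological, biomolecular, user interaction | yes |
| 2.8, end of modelling paragraph | baseline measures, blood markers, neurophysiological parameters | not listed |

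Two places include the app data and two leave them out. The word baseline in the last row may also qualify only the clinical measures: blood and TMS data are collected at both T0 and T1 (2.7), so the sentence does not clearly secure T0 values for them.

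**2. Timing.** The primary outcomes are changes from T0 to T1 (5 weeks) and to T2 (3 months), per 2.6.1. Treatment, and so app use, lies between T0 and T1. The app data therefore fall inside both change windows.

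**3. Content.** The exercises cover executive functions, memory, attention, orientation and language (2.5). MoCA and FCSRT test overlapping domains (2.6.1). Levels or accuracy reached would partly reflect cognition during treatment; session counts would reflect treatment received. App scores are still not MoCA or FCSRT scores.

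**4. Can a real baseline predictor lose its importance?** Let B be a baseline marker, U in-treatment performance and Y the change, all standardised, with B acting only through U. Assume paths of 0.5 (B to U) and 0.6 (U to Y).

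- Correlation of B with Y: 0.5 × 0.6 = 0.30.
- Coefficient of B with U in the model: (0.30 − 0.5 × 0.6) / (1 − 0.5²) = 0.

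A simulation with 400,000 records gave 0.299 and −0.001. The marker is informative before treatment and appears useless once U is included.

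**5. How much could accuracy change?** Assume normal variables and response defined as a median split of the change. A score with correlation ρ to the change has AUC = 0.5 + (2/π) × arcsin(ρ/√2).

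- With an uninformative baseline marker, the AUC from baseline alone is 0.50. Adding an in-treatment marker with ρ = 0.3, 0.5 or 0.7 gives 0.64, 0.73 or 0.83.
- With a baseline marker at 0.3, the AUC from baseline alone is 0.64. An independent in-treatment marker at 0.3, 0.5 or 0.7 gives combined ρ = √(0.3² + ρ²) = 0.42, 0.58 or 0.76, hence AUC 0.69, 0.77 or 0.86.

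Simulation reproduced these values to two decimals.

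**6. How small could it be?** The outcome is change, not the T1 level. With equal SDs and an assumed T0–T1 correlation of 0.8, a performance marker's correlation with change is (r with T1 − r with T0) / √(2 − 2 × 0.8).

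- 0.7 with both: 0 / √0.4 = 0, AUC 0.50.
- 0.7 with T1 and 0.6 with T0: 0.1 / 0.632 = 0.16, about 2.5% of variance, AUC 0.57.

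A baseline marker at 0.3 explains 0.3² = 9%, more than either. The documents do not show which case applies.

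**The case against.** The strongest reply is that the final sentence of the modelling paragraph is the specific one and governs. If so, no app data enter and the difficulty disappears. The Introduction supports that reading. But the article never says so, section 2.7 points the other way, and the sentence says what the dataset will include, not that it is limited to it.

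A second reply is that app data have legitimate uses. The Discussion sentence goes on to give even more weight to characterising the intervention procedures, the Conclusions foresee using progress and adherence to customise the programme, and section 2.8 speaks of factors associated with outcome. This stands: in-treatment data suit those purposes. It is a reason to report them separately, not to mix them with predictors of who benefits.

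A third reply is that detailed feature lists for an exploratory aim in a pilot belong in the full protocol or analysis plan. That is fair for an omission, but here the article makes two statements that do not agree.

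Finally, user interaction data are not defined, and T2 lies further from the app data than T1. Both points stand, and they limit any statement about size.

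**Conclusion.** The contradiction over the Aim 3 predictor set is real and should be settled before modelling. If the inclusive reading is followed, the resulting accuracy and SHAP ranking cannot answer, before treatment, which types of patients benefit most, and baseline predictors that act through in-treatment performance can be hidden. The mechanism follows from the timing and content of the data. Its size is unknown, since every correlation above is assumed.

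A reader might infer more than the documents support:

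- That the plan has settled on in-treatment predictors. It has not; two places leave them out.
- That app performance would dominate the ranking. This is not shown: for a change score its share may be near 0% to 2.5%, or much larger.
- That Aim 3 cannot identify likely responders at all. A T0-only model, which the text allows, is free of this objection.
- That the model is meant as a rule for offering treatment. The article speaks only of which types of patients benefit most and of helping to develop treatment pathways.

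**What to change.** Reconcile the third aim in the Introduction, the Aim 3 text in 2.7 and the modelling paragraph in 2.8 so that they name one predictor set. Restrict the main predictor-of-response model to variables measured at T0, and say explicitly that blood markers and TMS parameters enter with their T0 values only. Report any model that adds platform data (sessions, levels, accuracy) separately, labelled as an exploratory process or early-response analysis. The platform data need not be removed from all modelling.

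The cost is wording in three sections and one extra labelled analysis if the platform model is kept. No new data are needed. The downside is that the main model's reported accuracy may be lower than that of a model using everything collected.
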